**Methods/Design:**

The PIB will be a descriptive and analytical study employing mixed methods in which both quantitative and qualitative data will be systematically collected and analysed. The first wave will focus on 10 districts and primary data will be collected through interviews. The study seeks to interview 570 respondents of which 120 will be selected at national level with 40 based on each of the three policy domains, 200 from 10 randomly selected districts, and 250 from 50 facilities. Half of the respondents at each level will be randomly assigned to either face-to-face or on-line interviews. An integrated questionnaire for these interviews will collect both quantitative data through Likert scale-type questions, and qualitative data through open-ended questions. And finally focused dialogues will be conducted with selected stakeholders for feedback on the PIB findings. Secondary data will be collected using data extraction tools for performance statistics.

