#### Primary data

Both qualitative and qualitative data will be collected through a structured questionnaire with open and close ended questions administered to relevant stakeholders at macro, meso and micro-level of policy implementation (Table 3). The face-to-face collection of primary data will be facilitated by research assistants who will be trained on how to administer the questionnaires. Five research assistants will be deployed in each district. After completion at facility and district level, a selected number of research assistants from this pool will be assigned to conduct the interviews at national level.

**Table 3 Tab3:** Sample size estimates of key informants at various targeted levels

Data modules	Data source (10 districts) for the first round.	Overall sample size	Country specific sample sizes			
			National	District	Facility	Documents & HMIS-2 data
	*Study units*		*3 policy Areas*	*10 districts*	*50 facilities*	
	*Participants*					
Policy specific module 1. Malaria 2. Emergency obstetric care 3. Family planning	MOH programme officials National programmes DHMT and CSOs In-charge of facilities Programme managers in projects Health workers with related policy experience/roles	170	120 (40 per policy domain)	200 (20 per district	250 (at least 3 persons per facility)	• Programme documents • Policy documents • HMIS trends in the last 2 yrs. • Evaluations documents • Published literature • Government reports • Likert scale interviews with some open-ended questions • 6 modules of questions
Total unique respondents		570	120	200	250	
*Face-to-face interviews*		235	60	100	125	
*On-line interviews*		235	60	100	125	

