#### Questionnaire administration – On-line and face-to-face interviews

Through the two identified approaches, we seek to compare the on-line and face-to-face administration of the PIB questionnaires among the target groups. The purpose is to find the most effective way to interview respondents at the national, district and facility levels for the PIB. To inform future barometer surveys and to generate panel data to track trends in the key implementation domains, we will compare response rates, interview completeness and costs between on-line and face-to-face. A pool of respondents and their telephone contact at each level (national, district and facility) will be generated. From Table 3 half of the respondents will be assigned to either face-to-face or on-line interviews. Those that are assigned to fill on-line questionnaires will be requested to provide email addresses so that they can be invited to participate in the study. Within the email, a web-link to the survey will be provided. The survey will be hosted on the MakSPH server. To compensate respondents for the data and connectivity costs of filling the survey, a token of appreciation will be provided.

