##### At national level

respondents will be randomised by policy cluster (e.g. malaria, Family planning and emergency obstetric care). As we target to interview 120 persons at the national level i.e. 40 agencies/departments in each policy area, random allocation will be done to assign half to face-to-face interviews and half to on-line interviews. Before the random allocation, we will organise the second order organisations according to three policy domains to ensure a more balanced response across the three policy areas.

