##### At district level

Overall 10 districts will be selected from district clusters (strata) ranked in accordance with the district league table and will be shared with Ministry of Health during the inception stage of the survey. Following this general framework, the selection criteria below was generated and followed in the selection of the districts:i.Top fifteen performing districts according to the following clusters: national, regional, hard- to-reach districts, new districts and districts without regional referral hospitals,ii.Bottom fifteen performing districts in the same clusters in criteria (i) above,iii.Old districts expected to have fairly resilient health systems,iv.Peri – urban versus rural districts, andv.Districts where MakSPH has previously or is currently conducting activities with potential synergies with the PIB.

Using the above criteria, the districts selected to participate in this survey are: Arua, Jinja, Tororo, Hoima, Gulu, Kabarole, Kibuku, Kitgum, Ibanda and Wakiso.

Since there are 10 targeted districts for the PIB, respondents will be randomized using the district as a cluster – 5 districts for online and 5 district for face-to-face interviews. In addition to administration of the questionnaire at the district level, relevant routine data that cannot be collected at the national level will be also be collected.

The face-to-face survey will be conducted in 5 districts to be randomly selected from the 10 selected districts. The remaining districts will be assigned to on-line survey. In each district, interviews will target about 20 district level managers, and 20–25 facility level managers. In total (Table 3), we expect a sample of 570 respondents at the different levels of implementation.

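### Below national level the on-line versus face-to-face comparison is cluster-randomised, 5 districts against 5, but the abstract and the administration section describe assignment of respondents, and no balancing of the district draw is described

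*Protocol article*

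**What the plan says.** The abstract (Methods/Design) sets the sample at 570: 120 national respondents, 200 from the districts and 250 from the facilities. On mode it says: "Half of the respondents at each level will be randomly assigned to either face-to-face or on-line interviews". The section on questionnaire administration puts it the same way, without mentioning clusters: "half of the respondents will be assigned to either face-to-face or on-line interviews".

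The level-specific text differs:

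- **At national level**, within the three policy areas: "random allocation will be done to assign half to face-to-face interviews and half to on-line interviews".
- **At district level**: "respondents will be randomized using the district as a cluster", with five districts for each mode. The five face-to-face districts are drawn at random and the other five go on-line. Each district is to supply about 20 district managers and 20 to 25 facility managers.

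The ten districts are already named. The selection criteria include high and low league-table performance, and peri-urban against rural setting. Table 3 splits the sample by mode as 60/60, 100/100 and 125/125, and prints a total of 235 for each mode. The outcomes of the comparison are response rates, interview completeness and costs.

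**The concern.** The unit of randomisation determines how much a comparison can show. A reader of the abstract would take the mode comparison to rest on several hundred independently allocated people. Below national level it rests on ten units. Respondents in one district share connectivity, remoteness and management, all of which could plausibly affect whether an on-line invitation is answered and what a visit costs.

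Two things follow. First, a comparison that counted respondents as independent would give intervals that are too narrow. Second, with five districts per mode, a plain draw can by chance put most of the stronger or peri-urban districts on one side. Objective 4 is the only randomised comparison in the study and is meant to inform how later waves are conducted.

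**Working it through.** **Inputs from the protocol article.** Sample 120 + 200 + 250 = 570 (abstract, Table 3), which reproduces. Ten districts, five per mode (At district level). Cluster size (200 + 250)/10 = 45. No ICC, power or effect size is given.

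**Table 3 totals.** 60 + 100 + 125 = 285 per mode, and 2 × 285 = 570. The printed 235 does not reproduce: 2 × 235 = 470.

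**Share allocated by district.** 450/570 = 78.9%.

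**Effective sample size per mode.** Design effect DE = 1 + (45 − 1) × ICC, applied to the 225 per mode that follow their district. The 60 national respondents per mode are kept at DE = 1. Effective n = 60 + 225/DE.

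| ICC (assumed) | DE | 225/DE | Effective n | Share of 285 |
|---|---|---|---|---|
| 0.01 | 1.44 | 156 | 216 | 76% |
| 0.02 | 1.88 | 120 | 180 | 63% |
| 0.05 | 3.20 | 70 | 130 | 46% |
| 0.10 | 5.40 | 42 | 102 | 36% |

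With 40 per district, the lower end of the stated range, the design effects are 1.39, 1.78, 2.95 and 4.90, so the picture is much the same.

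**Precision in the 450, illustrated at an assumed 70% response rate.** If individuals were allocated, the 95% half-width for the difference would be 1.96 × √(2 × 0.21/225) = 8.5 points. On district summaries with 8 df it is 2.306 × √(2 × 0.21 × DE/225), which gives 14, 18 and 23 points at ICC 0.02, 0.05 and 0.10.

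**Respondent-level test in the 450, if one were used.** The true size of a nominal 5% test is 2 × [1 − Φ(1.96/√DE)] = 15%, 27% and 40% at the same three ICCs.

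**Balance of the draw.** There are C(10,5) = 252 possible draws. If five districts were top and five bottom performers (assumed), draws with a 4-1 or 5-0 split number 2 × C(5,4) × C(5,1) + 2 = 52, and 52/252 = 21%. Excluding them would leave 200 allowed draws, so a permutation test could still reach a two-sided p of 2/200 = 0.01.

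**The case against.** The strongest reply is that nothing is hidden. The district-level text says that "respondents will be randomized using the district as a cluster", no power or precision is claimed for any head-count, and no respondent-level test is specified. The analysis may be set out in a fuller document. Objective 4 is also one of five objectives in a largely descriptive survey. All of this stands. The false-positive rates above therefore show what a respondent-level test would do, not what the protocol plans. What remains is the conflicting description of the unit and a draw with no stated balancing.

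A reader might infer more than the document supports:

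- **That the protocol relies on 285 per mode.** It does not print that figure. 285 is the sum of Table 3's entries.
- **That the loss of information is always large.** That depends on the ICC. At 0.01 the loss is about a quarter.
- **That Table 3 contradicts the district-level text.** It does not: 5 × 20 = 100 and 5 × 25 = 125, so the split by mode fits whole districts.
- **That mode is confounded with district characteristics.** The draw is random, so the risk is chance imbalance, which a district-level analysis reflects in a wider interval.
- **That the staffing text conflicts with the design and distorts the cost comparison.** The sentence "Five research assistants will be deployed in each district" follows one about face-to-face collection and can mean the face-to-face districts only.
- **That mode should simply be allocated within districts.** This is a trade-off. It means visiting five more districts and mixing modes among colleagues when only on-line respondents receive a token.

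Two uncertainties remain. The national unit may be the person or the agency, because the text equates the two. The figure on the selection flow is not shown and may describe a restricted draw.

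**Conclusion.** The point holds as an inconsistency and a design weakness that should be fixed; it is not a false claim of power. The abstract and the administration section describe assignment of respondents, while the operative text allocates ten districts for 79% of the sample. Effective size per mode is about 216 to 102 of 285 for ICCs from 0.01 to 0.10. The ICC range and the independence of the national respondents are assumptions; only the direction, a loss for any positive ICC, needs no value for the ICC. The 21% imbalance figure rests on an assumed even mix of top and bottom performers, which the protocol does not state. Separately, the 235 per mode in Table 3 is an arithmetic discrepancy on the page.

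**What to change.** 1. In the abstract and the questionnaire administration section, describe the comparison as cluster-randomised by district below national level, in line with the district-level text.
2. Stratify or constrain the 5 v 5 draw on league-table position and peri-urban or rural status, and record the set of allowed allocations before drawing.
3. Compare modes for the 450 district and facility respondents on the ten district summaries, using a t test with 8 df or a permutation test over the allowed allocations. Treat the 120 national respondents as a separate stratum, and state whether the person or the agency is the unit there.
4. Reconcile the printed 235 per mode in Table 3 with its entries, which sum to 285.

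The cost is wording, a slightly more complex draw and wider stated precision. No interviews, districts or staff are added. Item 2 must be settled before the districts are drawn.

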### Data analysis and displays

All quantitative and qualitative data collected from secondary and primary sources will be used to construct the barometer measurement metrics for the selected policies or policy domains. Descriptive and comparative statistics will be calculated to show implementation progress by policy/programmeme areas. The analysis will be simple enough to be understood by decision makers but clear enough to show actual implementation gaps. Qualitative data collected through open-ended questions, will be analysed using the conventional content analysis (CCA) to establish the main underlying factors contributing to implementation of specific policies.

All indicators will be tested for validity and reliability and most importantly for the ease with which they can be generated using routine and administrative data. A dashboard or score card will be developed to display performance or progress of the first wave barometer assessment. Simple info-graphics will be developed in ways that allow for easy updates and analysis of future trends.

The value of a well-functioning PIB is that it may extend the value chain and transcend the current health issues, thus adding ‘forecasting’ to the (A) Prevention, (B) Treatment, and (C) Follow up chain. This includes identification of and planning for future health issues and using the barometer to measure the country’s effectiveness in terms of addressing them.

### Data dissemination and stakeholder engagement

Unlike traditional studies in which results are simply published in the form of technical reports and journal articles, the results of the first wave barometer survey will be used to actively engage with upstream, midstream and downstream stakeholders to effect necessary changes.

### Study limitations

The study is multi-faceted and is scheduled to be implemented in a few selected districts and not at all the districts. It might be possible that relevant contextual factors and actors might inadvertently be missed. However, the study will use secondary information from many more districts to assess implementation. The selected policies are not mutually exclusive meaning that some issues may overlap. However, attempts will be made to ensure that overlapping issues are isolated and discussed.

## Ethical considerations

All respondents to the study will sign consent forms that clearly indicate how confidentiality will be protected in the study. No names will be recorded and all participants will be coded (anonymised) before analysis and reporting of results. No one will be forced to participate and refusals will be recorded as such. The phone contacts of the participants will not be shared with others outside of this study and will only be used for delivery of the survey. Phone contacts and all identifiers (such as titles, office names, etc.) will be will be stripped off the data to avoid tracing responses to a particular interviewee. Although a token of appreciation €10.0 will be provided to on-line interviewees, this is to compensate for the cost of data bundles that will be used by the respondents while responding to the survey. This token payment will not be used to coerce the respondents – although it will be offered at the point when the respondent terminates the interview. The phone number to receive this token will be provided at the point of exit from the online survey. These phone numbers will be used only for paying the token and not linked to the data a respondent has provided during the survey.

## Discussion

We anticipate that this study will have two key contributions to the body of knowledge on policy implementation in Uganda and other low and middle income countries. First, it is the first known attempt to develop a systematic methodology for assessing progress in policy implementation and at the same time engaging relevant stakeholders for corrective action. So not only is the study seeking to identify gaps and constraints but to also facilitate effective policy implementation for impact. The idea is to have three waves of such barometer surveys during the life of the SPEED project which will allow for horning of the protocol in terms of stakeholder engagements, measurement metrics (both qualitative and qualitative), sources of data both primary and secondary and also use of online tools for wider involvement of participants and also for quick processing of the data for further engagements. Second, the study results will contribute to achievement of UHC objectives for Uganda by ensuring that the selected policy cases for the barometer are relevant to the UHC agenda and government priorities. Application of an accountability framework such as a policy implementation barometer will foster a sense of responsibility amongst implementers and upstream monitoring will therefore become more effective and hopefully the impact will improve.

Policies succeed or fail for a variety of reasons and this study seeks to unpack the drivers and bottlenecks in the implementation of specific policies towards UHC in Uganda−that is malaria, family planning and emergency obstetric care. These are transnational priority health areas affecting most countries in the sub-region meaning that the results of this study will potentially have far reaching benefits. We anticipate that the overall structural and systemic challenges of policy implementation will influence regional policy implementation support networks and agencies. A toolkit on the policy implementation barometer and a validated database of appropriate measurement metrics will be developed as by-products of the study. Clearly, there is no silver bullet to addressing policy implementation as countries differ in contexts and contexts change over time. What is critical is to have a system or culture of learning from implementation which the PIB seeks to engender in Uganda.

## Abbreviations

ABC: Abstinence, Behaviour Change, and Condoms
ANC: Antenatal care
ART: Anti-retroviral therapy
CCA: Conventional Content Analysis
DHIS: District health information system
DHMT: District Health Management Teams
DHO: District Health Office
EPI: Expanded Programme on Immunisation
HIV: Human Immunodeficiency Virus
ICCM: Integrated Community Case Management
IRS: Insecticide Residual Spraying
ITN: Insecticide-treated nets
MakSPH: Makerere School of Public Health
MOH: Ministry of Health
PIB: Policy Implementation Barometer
PIBA: Policy Implementation Barrier Assessment
PMTCT: Prevention of Mother to Child Transmission
SPEED: Supporting Policy Engagement for Evidence-based Decisions
TOC: Theory of change
UHC: Universal Health Coverage
